**12.3 Study product administration**

When preparing a VRC-HIVADV014-00-VP dose in a syringe and administering the dose, consideration should be given to the volume of solution that may remain in the needle after the dose is administered. The pharmacy and clinic staff are encouraged to work together to administer the dose specified in the protocol.

At sites where registered pharmacists are legally authorized to administer drug, the HVTU may choose to have the HVTU pharmacist administer the vaccinations.

**12.3.1 VRC-HIVDNA009-00-VP (DNA)**

All VRC-HIVDNA009-00-VP injections may be administered in either deltoid at each vaccination visit. A 1 mL injection of VRC-HIVDNA009-00-VP vaccine will be administered IM using the Biojector®.

The Biojector® 2000 Needle-Free Injection Management System will be used as directed by the Biojector® manufacturer. Neither the material being injected nor injection site skin preparation requires deviation from standard procedures. The injection site is disinfected and the area allowed to dry completely. The skin around the injection site is held firmly while the syringe is placed against the injection site at a 90° angle. The actuator is pressed and the material is released into the muscle. After the injection, the site is covered with a sterile covering and pressure applied. Biojector® utilizes sterile, single-use syringes for variable dose, up to 1 mL, medication administration. The study product is delivered under pressure by a compressed CO2 gas cartridge that is stored inside the Biojector®. When the Biojector's® actuator is depressed, CO2 is released, causing the plunger to push the study product out of the sterile syringe through the skin and into the underlying tissue. The study product is expelled through a micro-orifice at high velocity in a fraction of a second to pierce the skin. The CO2 does not come in contact with the injectate and the syringe design prevents any back splatter or contamination of the device by tissue from the subject.

### 12.3.2 VRC-HIVADV014-00-VP

#### Group 1 - Intramuscular (IM) injections

VRC-HIVADV014-00-VP intramuscular (IM) injections are to be given into either deltoid muscle as a volume of 1 mL using a 21 or 23 gauge needle with a length of 1 or 1-1/2 inch (depending on subject arm size) and using standard IM injection technique.

#### Group 2 - Intradermal (ID) injections

VRC-HIVADV014-00-VP intradermal (ID) injections are to be given as a volume of 0.1 mL using a 25-gauge needle with a length of 5/8 inch. The ID injections will be administered in the skin overlying the deltoid area of the arm. The needle will be inserted into the skin at a 15 degree angle to the skin and bevel side up until the bevel is seen to be fully under the skin. The needle bevel will then be rotated about 45 degrees. The syringe contents will be injected to form a small bleb. Rotating the bevel is intended to ensure that the needle bevel is fully under the skin and to reduce the chance of inadvertent leaking of the injectate during the injection.

#### Group 3 - Subcutaneous (SC) injections

VRC-HIVADV014-00-VP subcutaneous (SC) injections are to be given as a volume of 1 mL using a 23 gauge needle with a length of 1/2 inch and using standard SC injection technique. The SC injections will be given over the triceps area of the upper arm.

## 12.4 Study product acquisition

Study products will be provided by Vaccine Research Center, National Institutes of Allergy and Infectious Diseases, NIH.

At US HVTUs, the pharmacist can obtain VRC-HIVDNA009-00-VP and VRC-HIVADV014-00-VP from the NIAID Clinical Research Products Management Center (CRPMC) by following the ordering procedures given in the section on Study Product Control in *Pharmacy Guidelines and Instructions for DAIDS Clinical Trials Networks*.

At non-US HVTUs, the pharmacist can obtain VRC-HIVDNA009-00-VP and VRC-HIVADV014-00-VP from the NIAID Clinical Research Products Management Center (CRPMC). Once a non-US HVTU is registered for the study and all required documents have been received by DAIDS Pharmaceutical Affairs Branch, the Pharmacist can order product by following the procedures given in the HVTN 069 Study Specific Procedures (SSP).

## 12.5 Pharmacy records

The HVTU pharmacist is required to maintain complete records of all study products received from the CRPMC and subsequently dispensed. For US sites, all unused study products must be returned to the CRPMC after the study is completed or terminated. The procedures are included in the sections on Study Product Placebo and Drug Dispensing in *Pharmacy Guidelines and Instructions for DAIDS Clinical Trials Networks*. For non-US sites, specific instructions will be sent to the site after the study is completed or terminated.

The pharmacist of record is responsible for maintaining randomization codes and randomization confirmation notices for each participant in a secure manner.

## 13 Safety monitoring and review

### 13.1 Assessing reactogenicity

Reactogenicity assessments are performed for all participants following each vaccination. HVTU staff will assess reactogenicity according to standard HVTN procedures as specified in the HVTN MOP (Study Operations>Safety Assessment>Reactogenicity). Any procedures that vary from the HVTN standard will be defined in *HVTN 069 Study Specific Procedures*.

The reactogenicity assessment period is for 3 days following the day of vaccination. Participants are instructed to record symptoms using a post-vaccination symptom log. The site will make arrangements for daily reporting of reactogenicity events. Clinic staff will follow new or unresolved reactogenicity symptoms present at Day 3 to resolution. The schedule is shown in Table 13-1.

Assessments to be performed:

- Systemic symptoms: body temperature, malaise and/or fatigue, myalgia, headache, chills, arthralgia, nausea, vomiting
- Local symptoms (at the injection site): pain, tenderness
- Vaccine-related lesions: erythema, induration/swelling/edema
- Axillary lymph nodes (required only when reactogenicity assessments are performed by HVTU staff): lymph node tenderness, enlargement

**Table 13-1 Schedule of reactogenicity assessments**

| Day            | Time                                       | Performed by              |
|----------------|--------------------------------------------|---------------------------|
| 0 a | Baseline: before vaccination               | HVTU staff                |
|                | Early: 25 to 45 minutes after vaccination  | HVTU staff                |
|                | Between early assessment and 11:59pm Day 0 | HVTU staff or participant |
| 1              | Between 12:00am and 11:59pm Day 1          | HVTU staff or participant |
| 2              | Between 12:00am and 11:59pm Day 2          | HVTU staff or participant |
| 3 b | Between 12:00am and 11:59pm Day 3          | HVTU staff or participant |

aDay of vaccination

bNew or unresolved reactogenicity symptoms present on Day 3 are followed until resolution

Participants are encouraged to contact the clinic for events that arise during the period between vaccination and the next scheduled visit.

### 13.2 Grading adverse events

Local and systemic signs and symptoms are assessed and graded based on *The Division of AIDS Table for Grading the Severity of Adult and Pediatric Adverse Events* (DAIDS AE Grading Table), Version 1.0, December, 2004, available on the RCC website at <http://rcc.tech-res-intl.com>.

### **13.3 Adverse event reporting and safety pause/expedited Protocol Safety Review Team (PSRT) review rules**

All adverse events are reported to the SDMC on the appropriate case report form (CRF) according to procedures in the HVTN MOP (Study Operations>Safety Assessments>Adverse Experiences). The mechanism of reporting certain Grade 3 and higher grade vaccine-related symptoms and adverse events to the SDMC Clinical Affairs staff is depicted in Table 13-2. The mechanism of reporting SAEs and other events meeting expedited adverse event (EAE) reporting requirements to DAIDS is specified in Section 13.4.

#### **13.3.1 Adverse events to which safety pause/expedited PSRT review rules apply**

The adverse events applying toward a safety pause or PSRT expedited review are shown in Table 13-2. In order to be counted toward a safety pause or PSRT expedited review, adverse events must be vaccine related. “Vaccine related” means the event is judged to be possibly related, probably related, or definitely related to the study vaccination. Symptoms reported on a reactogenicity CRF are assumed by the SDMC to be vaccine related unless determined to have unequivocal alternate etiology.

#### **13.3.2 Adverse event reporting**

Notify the SDMC Clinical Affairs staff of adverse events as indicated in Table 13-2.

Telephone numbers and e-mail addresses are listed in the *HVTN 069 Study Specific Procedures*, Key Resource Guide, and can be used to notify SDMC Clinical Affairs staff of any serious safety concern requiring their attention. Concerns requiring immediate attention should be communicated by telephone.

In the case of e-mail notification, SDMC Clinical Affairs staff will reply during working hours (US Pacific Time) to confirm that the e-mail has been received and reviewed. If e-mail service is not available, the HVTU will notify SDMC Clinical Affairs of the event by telephone, then submit case report forms.

Case report forms should be faxed within the timeframes indicated in Table 13-2.

#### **13.3.3 Expedited PSRT review and safety pause**

If an expedited PSRT review is triggered, the SDMC Clinical Affairs staff notifies the HVTN 069 PSRT as soon as possible during working hours (US Pacific Time)—or, if the information was received during off hours, by the morning of the next work day—that a PSRT AE review is needed. If a PSRT AE review cannot be completed within 48 hours of SDMC notification (excluding weekends and US federal holidays), an automatic safety pause occurs.

For all safety pauses, the SDMC Clinical Affairs staff notifies the PSRT, DAIDS Pharmaceutical Affairs Branch (PAB), Regulatory Compliance Center (RCC)/Regulatory Affairs Branch (RAB), and participating HVTUs that all enrollment and vaccination with the product related to the event that triggered the pause will be held until further notice. When an immediate safety pause is triggered, the SDMC Clinical Affairs staff also notifies the HVTN SMB; RAB notifies the US FDA.

Vaccinations may be suspended for safety concerns other than those described in Table 13-2, or before pause rules are met, if in the judgment of the PSRT, participant safety may be threatened.

Adverse events that do not prompt a safety pause or a PSRT expedited review are routinely reviewed by the PSRT (Section 13.7.2).

**Table 13-2 Adverse event notification and safety pause / expedited PSRT review rules**

| Rule | Toxicity | Symptom/AE                                                                                                                                                                                                                                                      | Vaccine relatedness               | HVTU action                                           | SDMC action              | Criterion for SDMC action                  | Criterion for each subsequent SDMC action                      |
|------|----------|-----------------------------------------------------------------------------------------------------------------------------------------------------------------------------------------------------------------------------------------------------------------|-----------------------------------|-------------------------------------------------------|--------------------------|--------------------------------------------|----------------------------------------------------------------|
| 1    | Grade 4  | Any lab abnormality, adverse event, local or systemic reactogenicity symptom                                                                                                                                                                                    | Probably or definitely            | Phone and email immediately and fax forms immediately | Immediate pause          | 1 ppt with AE/symptom at specified grade   | 1 additional ppt with the same AE/symptom at specified grade   |
| 2    | Grade 4  | Any lab abnormality, fever, vomiting, localized injection site necrosis or other clinical adverse event other than subjective reactogenicity symptoms                                                                                                           | Possibly                          | Fax forms within 24 hours                             | Expedited PSRT AE review | 1 ppt with AE/symptom at specified grade   | 1 additional ppt with the same AE/symptom at specified grade   |
| 3    | Grade 3  | Any lab abnormality, fever, vomiting, localized injection site reaction other than pain or tenderness (ulceration, secondary infection, phlebitis, sterile abscess, or drainage), or other clinical adverse event other than subjective reactogenicity symptoms | Possibly, probably, or definitely | Fax forms within 24 hours                             | Expedited PSRT AE review | ≥2 ppts with AE/symptom at specified grade | ≥2 additional ppts with the same AE/symptom at specified grade |

For AE descriptions and grading, see *The Division of AIDS Table for Grading the Severity of Adult and Pediatric Adverse Events* (DAIDS AE Grading Table), Version 1.0, December, 2004.

Phone numbers and e-mail addresses are listed in *HVTN 069 Study Specific Procedures*, Key Resource Guide.

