#### **13.5.2 Stopping vaccinations for a participant**

Under certain circumstances, an individual participant's vaccinations will be stopped. Such participants should be encouraged to participate in follow-up visits and all protocol-related procedures (unless medically contraindicated) per the protocol for the remainder of the trial.

Specific events that will result in stopping a participant's vaccination schedule include the following:

- Clinically significant condition (i.e., a condition that affects the immune system or for which continued vaccinations and/or blood draws may pose additional risk), including but not limited to the following:
  - HIV infection (requires termination from the study)
  - Pregnancy (regardless of outcome)
  - Any Grade 4 local or systemic symptom, lab abnormality, or adverse event, that is subsequently confirmed to be *possibly*, *probably*, or *definitely* related to vaccination
  - Any Grade 3 lab abnormality or other clinical adverse event (exception: fever or vomiting and subjective local and systemic symptoms) that is subsequently confirmed to be *possibly*, *probably*, or *definitely* related to vaccination
  - Type 1 hypersensitivity associated with vaccination
- Inability to receive vaccination within the specified period for the designated study visit (see *HVTN 069 Study Specific Procedures*)
- Investigator determination in consultation with the study chair and statistician (e.g., for repeated nonadherence to study staff instructions)

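### Table 13-2 has no rule for a Grade 4 subjective reactogenicity symptom judged possibly related, although section 13.5.2 stops that participant's vaccinations

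*Protocol*

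**What the plan says.** Table 13-2 (Protocol section 13.3.3) has three rules.

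- **Rule 1**, Grade 4, probably or definitely related. Scope: "Any lab abnormality, adverse event, local or systemic reactogenicity symptom". One participant causes an immediate pause, and the site phones, emails and faxes at once.
- **Rule 2**, Grade 4, possibly related. Scope: "Any lab abnormality, fever, vomiting, localized injection site necrosis or other clinical adverse event other than subjective reactogenicity symptoms". The site faxes forms within 24 hours, and one participant triggers expedited PSRT review.
- **Rule 3**, Grade 3, any of the three relatedness levels. Its scope includes laboratory abnormalities, fever, vomiting and "localized injection site reaction other than pain or tenderness (ulceration, secondary infection, phlebitis, sterile abscess, or drainage), or other clinical adverse event", again without subjective reactogenicity symptoms. The site faxes each event within 24 hours. Expedited review starts at two or more participants.

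Section 13.5.2 governs the individual. Vaccinations stop for "Any Grade 4 local or systemic symptom, lab abnormality, or adverse event, that is subsequently confirmed to be" possibly, probably or definitely related. Its Grade 3 criterion has a carve-out: "exception: fever or vomiting and subjective local and systemic symptoms". The Grade 4 criterion has none.

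Section 13.3.1 counts possibly related events as vaccine related for the purposes of the table, and adds: "Symptoms reported on a reactogenicity CRF are assumed by the SDMC to be vaccine related unless determined to have unequivocal alternate etiology". It does not say at which of the three levels. Section 13.3.2 directs sites to the table for what they must notify and how quickly.

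**The concern.** Expedited review protects the participants who have yet to receive the product. For subjective reactogenicity symptoms at Grade 4, the table goes from no action at possibly related to an immediate trial pause at probably related. The intermediate step that every other Grade 4 event gets, a prompt fax and an expedited review, is missing. As written, any number of participants could have such an event without the table calling for either.

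Section 13.5.2 suggests that the protocol discounts subjectivity at Grade 3 but not at Grade 4. Rule 3 fits that pattern and Rule 2 does not.

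The setting gives this some weight. Section 4 reports no human data for this Ad5 vaccine by the intradermal or subcutaneous route and names VRC 011 as the trial that will begin to collect them. Section 4.3.2 notes that reactogenicity at this dose may be somewhat greater when the vaccine is given as a booster, and Table 4-4 shows moderate systemic symptoms in 6 of 14 booster recipients. The severe reactions listed for HVTN 054 (section 4.2.2) were mostly of the subjective kind: malaise or fatigue in 4 participants, chills in 3, myalgia in 2 and headache in 1, with one Grade 3 fever. They arose in the group given 10^11 PU or placebo, an active dose ten times the present one, and none is described as Grade 4. They show the type of event and not a rate.

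**Working it through.** The plan states no figure to reproduce. The check runs through every combination of grade, symptom type and relatedness, and applies Table 13-2 and section 13.5.2 to each.

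**Grade 4**: 3 relatedness levels × 2 types (subjective reactogenicity symptom, or any other event) = 6 cells.

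| Type | Relatedness | Table 13-2 | 13.5.2 |
|---|---|---|---|
| Other | Possibly | Rule 2 | Stop |
| Other | Probably | Rule 1 | Stop |
| Other | Definitely | Rule 1 | Stop |
| Subjective | Possibly | **No rule** | Stop |
| Subjective | Probably | Rule 1 | Stop |
| Subjective | Definitely | Rule 1 | Stop |

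Table 13-2 acts in 1 + 4 = 5 of 6 cells (Rule 2 in one, Rule 1 in four). Section 13.5.2 acts in 6 of 6.

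**Grade 3, subjective symptoms**: 3 cells. Rule 3 excludes them and 13.5.2 exempts them, so each acts in 0 of 3. For subjective symptoms, the two sets of rules therefore part company in one cell only: Grade 4, possibly related.

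**Does section 13.3.1 close that cell?** It presumes that symptoms on the reactogenicity form are vaccine related, but vaccine related there spans all three levels. A symptom presumed related may still sit at possibly, so the presumption does not by itself bring it under Rule 1. If the data center applied the presumption at probably, the cell would seldom be reached. The protocol does not say which is done.

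**Comparison at the same relatedness.**

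| Event, possibly related | Site action under the table | Expedited PSRT review |
|---|---|---|
| Grade 3 laboratory abnormality | Fax each event within 24 hours | At 2 or more participants |
| Grade 4 laboratory abnormality | Fax within 24 hours | At 1 participant |
| Grade 4 subjective symptom | None | None |

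**After the change.** With Rule 1's event scope in Rule 2, the open cell falls under Rule 2 and the table acts in 6 of 6 Grade 4 cells. Grade 3 is unchanged.

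These counts describe what the table covers. They do not measure risk.

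**The case against.** The strongest defense is that the exclusion was chosen. Section 13.3 introduces the table as covering only certain events of Grade 3 and above. The words excluding subjective symptoms appear in Rules 2 and 3 and are absent from Rule 1, which looks like drafting intent. Stopping one person and reviewing a whole trial serve different purposes, so a lower threshold for the individual is coherent. The two sets of rules also differ elsewhere: at Grade 3, Rule 3 counts fever and vomiting while 13.5.2 exempts them, and 13.5.2 acts on one participant where Rule 3's review needs two. All of this stands. A reader might infer that the table contradicts 13.5.2; for these reasons the text does not support that.

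A reader might also infer that such an event would go unnoticed. It would not. On reactogenicity, section 13.1 states: "The site will make arrangements for daily reporting of reactogenicity events". Section 13.3.2 gives a telephone route for serious concerns. Section 13.3.3 sends events outside the table to routine PSRT review and lets the PSRT suspend vaccination before any pause rule is met. Section 13.7.2 sets weekly review in the injection phase. The DAIDS expedited reports (13.4) and the daily data-center review (13.7.1) may also catch the event, but 13.7.1 is limited to serious events, events needing expedited DAIDS reporting, and events meeting pause criteria. Whether this event would qualify depends on a manual that is not shown.

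These safeguards make the consequence small, but they do not replace the missing trigger. Suspension is discretionary and depends on the PSRT knowing of the event, the routine review is weekly, and section 13.1 does not say that the daily reports reach the data center or the PSRT. None of them is a time-limited trigger at one participant. The protocol gives no reason for applying the exclusion at Grade 4.

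**Conclusion.** The gap is real on the text, and it is minor. One cell of the pause table, Grade 4 subjective symptoms judged possibly related, has no rule, while its neighbors in both directions do. It is best described as a safety trigger out of step with the protocol's own Grade 4 threshold for individuals. It affects no sample size, power or error rate.

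Two further inferences should be resisted. A reader might count how many of the symptoms solicited in section 13.1 fall into the cell. The documents do not settle that: subjective is not defined, axillary node tenderness is also solicited, and whether each symptom has a Grade 4 definition depends on the DAIDS grading table, which is not shown. A reader might also infer that such events are to be expected. The safety summaries report no Grade 4 subjective event. The closest experience, HVTN 057 (the same Ad5 dose as a boost after the same DNA vaccine, still blinded), is described as generally mild and sometimes moderate. No frequency is claimed here.

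The conclusion assumes that relatedness for reactogenicity symptoms can be recorded as possibly. The wording of 13.3.1 allows this, but operating procedures that are not shown might narrow it.

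**What to change.** In Table 13-2, replace the event scope of Rule 2 (Grade 4, possibly related) with that of Rule 1: "Any lab abnormality, adverse event, local or systemic reactogenicity symptom". One such event then leads to forms faxed within 24 hours and expedited PSRT review, and each additional participant with the same symptom triggers a further review under Rule 2's existing criterion. Merely deleting the closing exclusion from Rule 2 would be less clear, because Rule 1 lists reactogenicity symptoms separately from adverse events and Rule 2 would still not name them.

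Keep the exclusion of subjective symptoms in Rule 3, where it agrees with the Grade 3 exemption in 13.5.2. Section 13.3.1 needs no change.

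The change is to one table cell and adds no visits, samples or data items. Its cost is a rare extra expedited review. Under section 13.3.3 that review becomes an automatic safety pause if it is not completed within 48 hours of data-center notification, weekends and US federal holidays not counted.

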### 13.3.4 Review and notification following safety pause

The PSRT reviews safety data and decides whether the pause can be lifted or permanent discontinuation of vaccination is appropriate, consulting the SMB and the US FDA if necessary. DAIDS will consult with the US FDA for all immediate safety pauses. SDMC Clinical Affairs staff notifies participating HVTUs, PAB, and RCC/RAB of the decision regarding resumption or discontinuation of study vaccinations. SDMC Clinical Affairs staff also notifies the HVTN SMB, and RAB notifies the FDA, if these groups have not been informed earlier.

Each HVTU is responsible for submitting to its IRB/IEC, and to any local regulatory authority, protocol-related safety information (such as IND safety reports, notification of vaccine holds due to the pause rules, etc.) as required.

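### Table 13-2 has no row for death, so a fatal event graded 4 and judged possibly related leads to an expedited review, not an immediate pause

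*Protocol*

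**What the plan says.** Table 13-2 has three rules.

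- **Rule 1:** Grade 4, probably or definitely related. The site phones, emails and faxes at once, and one participant is enough for an immediate pause.
- **Rule 2:** Grade 4, possibly related, with the scope "Any lab abnormality, fever, vomiting, localized injection site necrosis or other clinical adverse event other than subjective reactogenicity symptoms". The site faxes forms within 24 hours, and one participant triggers an expedited PSRT review.
- **Rule 3:** Grade 3, at least possibly related, in two or more participants. This also triggers an expedited PSRT review.

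Section 13.3.3 adds a default: if the review "cannot be completed within 48 hours of SDMC notification (excluding weekends and US federal holidays), an automatic safety pause occurs". In any pause, "all enrollment and vaccination with the product related to the event that triggered the pause will be held until further notice". The PSRT also has discretion: "Vaccinations may be suspended for safety concerns other than those described in Table 13-2, or before pause rules are met".

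On notification, Section 13.3.3 states: "When an immediate safety pause is triggered, the SDMC Clinical Affairs staff also notifies the HVTN SMB; RAB notifies the US FDA". Section 13.3.4, on what follows a pause, adds: "SDMC Clinical Affairs staff also notifies the HVTN SMB, and RAB notifies the FDA, if these groups have not been informed earlier".

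Grading is left to an external document. Section 13.2 says "Local and systemic signs and symptoms are assessed and graded based on" the DAIDS grading table. The protocol does not reproduce that table or say how it grades death.

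**The concern.** The cause of a single early death is often unclear, so *possibly* is a plausible first rating. On that rating Table 13-2 gives a review while dosing continues, where *probably* would have stopped dosing at once.

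Elsewhere the protocol treats *possibly* as enough. Section 13.3.1 counts it as vaccine related, and Section 13.5.2 stops a participant's own vaccinations for a Grade 4 event confirmed as possibly related. Only the trial-wide pause separates the two ratings.

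The participants are healthy volunteers, and two of the three boost routes are new for this product. Section 4 describes the first trial of the Ad5 vaccine by the intradermal (ID) and subcutaneous (SC) routes as not yet open. Section 1.2 knows of no report of any recombinant adenoviral vector given SC. At stake are further injections of the implicated product before anyone has decided whether it is safe to go on.

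**Working it through.** The protocol gives no figure to reproduce. The check has two parts: tracing a death through the table, and sizing the delay.

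**Trace of a fatal event**

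1. Graded 4, probably or definitely related: Rule 1, immediate pause.
2. Graded 4, possibly related: the relatedness column excludes Rule 1. Rule 2 applies, because a death is a clinical adverse event and not a subjective reactogenicity symptom. The result is a fax within 24 hours and an expedited review, with no immediate pause.
3. Rule 3 is for Grade 3 and two or more participants, so it does not help.

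Sections 13.2 to 13.7 contain no separate pause rule for death.

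**Delay from site awareness to a pause, case 2**

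- PSRT suspends at once: 0.
- Site telephones at once and the full review limit is used: 48 h = 2 working days.
- Full fax limit also used, assuming that it runs from site awareness: 24 h + 48 h = 72 h = 3 working days.
- Section 13.3.3 lets the statistical and data management center pass on information received out of hours by the next work-day morning, so 3 working days is not a maximum.

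**Ad5 injections given in that time**

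Inputs: 90 participants with one Ad5 boost each (Schema), so 90 doses. Assumptions: even spread over 13, 26 or 52 weeks, and 5 clinic days a week. Formula: 90 / (weeks × 5) × days.

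| Boosting period | 2 working days | 3 working days |
|---|---|---|
| 13 weeks | 90/65 × 2 = 2.8 | 90/65 × 3 = 4.2 |
| 26 weeks | 90/130 × 2 = 1.4 | 90/130 × 3 = 2.1 |
| 52 weeks | 90/260 × 2 = 0.7 | 90/260 × 3 = 1.0 |

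The 90 × 3 = 270 DNA doses are not counted. They would matter if the DNA vaccine were the implicated product.

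**How rare is the trigger?** Section 8.4.1 gives serious adverse event rates in controls of about 1% (HVTN trials) and 3.5% (AVEG trials). In 90 participants that is 90 × 0.01 = 0.9 to 90 × 0.035 = 3.15 events of any kind and cause. The documents give no rate for related deaths, which would be only a small part of these.

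**The case against.** **The tiering is deliberate and consistent.** This stands. Matching the response to relatedness is coherent, and Rule 2 still acts on a single participant, with a pause by default if the review is late. The point is an improvement to a stated rule and does not show that the rule is wrong.

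**Other safeguards exist.** This also stands. The PSRT may suspend at any time. Section 13.3.2 says "Concerns requiring immediate attention should be communicated by telephone". Serious events are reviewed daily (13.7.1) and reported on an expedited basis to DAIDS (13.4), which is the IND sponsor. Section 13.3.4 refers to IND safety reports. The Safety Monitoring Board (SMB) reviews individual serious event reports and holds special reviews on request (13.7.4). These narrow the gap, but none is an automatic immediate pause.

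**The novelty of the routes can be overstated.** This is partly right. Section 1.2 reports nine volunteers given another Ad5-based vector ID with no adverse effect attributed to it. It also presumes that vaccine given intramuscularly reaches subcutaneous tissue. The stated ID doses were 8×10^7 or 8×10^8 PU, however, and the dose here is 10^10 PU, which is 12.5 times the higher one.

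Two stronger readings are tempting, and the documents support neither.

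- *A reader might infer that death is graded above 4, so that no row covers it at all.* The protocol does not show this. Section 13.3 speaks of Grade 3 and higher and Table 13-2 stops at Grade 4, which fits Grade 4 being the top category without proving it.
- *A reader might infer that the SMB and FDA would not hear of such a death.* It is true that the notice in Sections 13.3.3 and 13.3.4 hangs on a pause, so a timely review without one does not trigger it. But reports to the IND sponsor, IND safety reports and SMB review of serious events do not depend on a pause.

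**Conclusion.** The point holds as an optional, low-cost improvement. As written, a death graded 4 and rated possibly related leads to review and not to an immediate pause, and dosing continues by default unless the PSRT steps in.

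The exposure is small: roughly 0.7 to 4.2 further Ad5 injections over 2 to 3 working days, none if the PSRT acts at once, and more if an out-of-hours relay lengthens the delay. These counts rest on the assumed boosting period, and the trigger would be rare. The conclusion for Rule 2 assumes that death is graded 4. The remedy does not need that assumption, because it is keyed to the outcome and not to the grade. Sample size, power and type I error are not affected.

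**What to change.** Add one row at the top of Table 13-2:

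- **Toxicity:** death, whatever grade is recorded.
- **Symptom/AE:** any fatal event.
- **Relatedness:** possibly, probably or definitely.
- **Site action:** phone, email and fax forms immediately.
- **SDMC action:** immediate pause.
- **Criterion:** 1 participant, and 1 additional participant for each later action.

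Insert *non-fatal* in Rule 2. The notice to the SMB and FDA in Section 13.3.3 and the DAIDS consultation with the FDA in Section 13.3.4 then apply without new text.

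The drafting cost is trivial, but the operational cost is not zero. A death that proves unrelated would still hold enrollment and vaccination with the implicated product until the PSRT lifts the pause under Section 13.3.4. Section 13.5.1 bars vaccination outside the visit window, and under Section 13.5.2 a missed window stops that participant's vaccination schedule. A long hold could therefore cost some participants the Ad5 boost and with it the primary immunogenicity endpoint. Section 8.4 allows for 10% missing endpoint data, which is 9 of 90 participants or 3 of 30 per arm. A prompt PSRT decision after such a pause keeps this cost small.
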